**1. THE NEED FOR A TRIAL**

**1.1 Problem:**Amputation of the lower limb (LLA) can be devastating. At the individual level it reduces physical, emotional, and social wellbeing; while contributing to a significant burden on the healthcare system. In 2017, Imam and Nominated Principal Applicant (NPA) **[name]** et al., reported that 7,300 Canadians have a LLA each year-- mostly (85%) occurring in >50 years of age.3 The primary cause of LLA was related to diabetes and vascular complications (91%),3 and most (~70%) LLA occurred in men.3 For many patients, undergoing an LLA predicts poor health outcomes.4 Women are more likely to be readmitted to hospital compared to men, due to complications after LLA,4 because of greater risk of morbidity and mortality after LLA including a higher risk for falls.5-7 Women also experience more psychological and social challenges,8-10 including a lack of confidence,7, 11 fear of falling,7, 12 depression7, 13 and pain.8 Combined or alone, these factors create critical barriers to independence in daily tasks (e.g., toileting) and engagement in social activities (e.g., meeting friends, volunteering).7 Taken together, LLA is a significant life event, that requires a wholistic approach during recovery to address both physical and psychological barriers post LLA to maximize a person’s autonomy and quality of life. Additionally, the COVID-19 pandemic has impacted the delivery and accessibility of healthcare services.

Canadian cost estimates of LLA are not available, but the projected lifetime cost of an LLA per person was estimated (in 2002) at US $509,000.14 The cumulative

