**1.4 How the results will be used:** Currently adults with LLA receive fewer hours of rehab than is considered best practice, and limited management post-discharge.18 This reduction in care creates a gap in the consolidation of skills and understanding, potentially leading to decreased mobility, functional independence, quality of life,19, 56 and a significant healthcare cost.14-17 SMART has the potential to address the gap and improve LLA outcomes. Our study will enable us to assess the clinical effectiveness, and key implementation factors, of SMART with a sample of people with LLA, with attention given to sex, gender and cause of amputation. In sum, it will provide essential information for integration of SMART into clinical practice, if appropriate.2 This study will provide us with a better understanding of the effects of SMART on walking capacity and relevant outcomes, while observing and gathering information on implementation of SMART in two provinces (BC and ON).

Beyond the potential for scale up and spread of SMART as a clinical innovation, we anticipate the results will be of interest to clinicians locally and nationally. As eHealth is relatively new as an intervention in clinical practice beyond post-amputation, we anticipate our methods will be of interest to other clinical areas. We also anticipate the findings from this study will provide valuable information on service provision via eHealth during the COVID-19 pandemic. Therefore, for our end-of-grant KT strategies we will disseminate findings via websites (e.g., health authorities in BC and ON), electronic and print newsletters (e.g., Physiotherapy Association of BC and ON), blogs, present at provincial practice forums, national webinars, and through social media (e.g., Twitter). We will build on our existing partnerships to reach members of relevant associations, such as the International Society of Prosthetics and Orthotics Canada, and provide summaries for their websites and electronic newsletters. We will submit abstracts to international conferences (e.g., International Society of Prosthetics and Orthotics World Congress), and manuscripts will be submitted for publication. We will work with our patient partners to share plain language summaries with other adults with LLA via newsletters, social media and websites (e.g. Amputee Coalition of BC).

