**2.4 Protecting against bias - Blinding:**Blinding of participants for the RCTs on the effect of eHealth interventions is impossible because of nature of intervetnions.66 Therefore, it is difficult to blind participants to the intervention received. The assessors will be blinded to group allocation, we will complete the primary outcome (TUG and ASCQ) first, and participants will be asked not to disclose their group allocation during assessments.66 Furthermore, we will have separate trainers for each group (to minimize trainer bias); and the primary outcome measure, the TUG is a performance-based measure with standardized instructions. Finally, all statistical analyses will be conducted by a blinded statistician.

**2.5 Inclusion and Exclusion Criteria:**To be included, participants will: have a unilateral dysvascular- or diabetic- related LLA (transtibial or transfemoral);3have conducted the casting for their initial prosthetic limb (up to 2 years); be aged ≥ 50 years (85% of adults with LLA);3 have a computer or tablet and have access to the internet, and self-identify as being able to speak and read English. We will exclude adults with substantial health conditions (e.g., congestive heart failure, diagnosed dementia); those anticipating further surgery (e.g. LLA revision) as identified by our study sites’ physiatrists; and an ability to use a tablet (e.g./ using hands for typing). Given these criteria, the results of this study will not be generalizable to all adults with LLA such as the very young and those who do not speak English. As most people with LLA are >50 years old and more than 90% of the population of BC and ON speak English, we are confident of obtaining a representative sample.

**2.6 Duration of Intervention:**Participants in the SMART group will receive the intervention for six weeks. Participants in the control group will be contacted weekly for a similar 6 week period.

**2.7** **Frequency and Duration of Follow-up:**There are six weekly SMART modules with each taking approximately 20 to 30 minutes to complete. Individuals will be encouraged to complete one module a week to reduce any perceived burden, and gradually integrate the information. Participants from both groups will receive a weekly contact: SMART group participants will receive a 20 minute telephone call/Zoom video call from peers, and the Control group participants one email or phone call by trainer.

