***Implementation:*** Following the [RE-AIM](http://www.re-aim.org/) framework,60 five elements of implementation will be assessed including, reach (target population), effectiveness (effects of SMART), adoption (by setting/staff), implementation (dose delivered and received, fidelity to the intervention), and maintenance of the behavior (in target population and settings). During study, the research coordinator will keep the detailed logs to monitor fidelity to research protocols and review the online chart for the adherence to the SMART (dose). Moreover, ***participant experience*** will be identifiedwith a brief30-minute audio-recorded semi-structured in-person interview with men and women (n=20) from the experimental group (*Section 2.2*) by the researcher at the end of the study (T3) to explore the experience and acceptability of the SMART program, health related goals, and any perceived disadvantageous of SMART. Moreover, we will call any dropout participants to obtain their feedback.

***Sociodemographic and Clinical Characteristics***: We will collect descriptive characteristics at T1 (**Appendix E**) including, age, sex, gender, level of education, marital status, weight, height, and clinical variables, such as presence of comorbidities, level, cause, side, and date of amputation, discharge date, date in which prosthetic training has been started, and date in which patient received the permanent prosthesis. We will also collect the participants’ self-report encounters with outpatient rehab care providers (e.g., PT, OT) and surgical consultations throughout the six-week intervention.

A cognitive screen, the Montreal Cognitive Assessment (MoCA) will be used to screen for cognitive impairments.

**2.9 Measuring outcomes at follow-up:** We will collectdata for intervention and control groups at three time points (**Appendix E**): T1=baseline; T2=within one week of completing SMART intervention; T3=retention period of four weeks post-intervention. The one-on-one semi-structured interviews with the SMART group to determine impressions of the protocol and intervention will be conducted at T3. All data collection will occur through online survey link on Qualtrics platform hosted by University of British Columbia. All sessions will be performed on Zoom video call.

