**2.10 Sample Size:**Our sample size calculation is based on identifying SMART is more effective than standard care from a clinical point of view (Clinical Superiority design),75 and minimize any potential waste of resources.76 We are planning to compare the 2-MWT using a ratio 1:1. In a previous study, the mean (SD) of clinically important change in distance walked in 2 minutes at discharge from the rehab facility was 13.6 (19.9) m in adults with unilateral LLA (mean age = 66 y).37 Assuming minimum important difference of 13.6 m, we will need to enroll a minimum 34 participants per group to be enable to reject a null hypothesis of no difference in means of walking capacity between the 2 groups with 80% power. The type-I error probability associated with this 2-sided test of the null hypothesis is 0.05. Our sample size is based on the feasibility of recruiting 2 adults aged over 50 years with an LLA, per site within 18 months, and with 68 participants at final assessment (accounting for participant attrition) we can have enough power to detect a difference in the primary outcome, i.e., 2-MWT. Acknowledging the challenges with participants,77 20% attrition rate, and non-compliance rate in RCTs, we will recruit 82 participants (41 per arm including both men and women).The target sample size will also facilitate estimates for adherence, and the number of participants with certain covariates (e.g., sex, gender), and inform the sample size calculation and stratification for the implementation study.

**2.11 Health services research issues:** Cost and cost-effectiveness of eHealth interventions have been demonstrated for patients with chronic disease conditions.78 However, we will not do a formal cost analysis in this study.

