**2.18 Sub-group analyses:**We will do a sub-group analysis to assess the differences in outcomes regards to sex, gender and amputation cause (Diabetes and dysvasuclar vs. others).

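### Sections 2.5 and 2.18 contradict each other on amputation cause: eligibility leaves the 'others' level of the planned subgroup contrast with 0 of 82 participants

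*Protocol*

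**What the plan says.** Section 2.18 of the Protocol names three subgroup factors: sex, gender and "amputation cause (Diabetes and dysvasuclar vs. others").

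Section 2.5 limits entry by cause. Participants must "have a unilateral dysvascular- or diabetic- related LLA (transtibial or transfemoral"). The same section sets out limits on generalisability: the results "will not be generalizable to all adults with LLA such as the very young and those who do not speak English". It gives age and language as examples and does not mention cause.

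Three other places bear on the point:

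- Section 1.1 treats diabetic and vascular causes as one category: "The primary cause of LLA was related to diabetes and vascular complications (91" per cent).
- Section 1.4 says the trial will be carried out "with attention given to sex, gender and cause of amputation".
- Section 2.8 lists, among the baseline (T1) variables, "level, cause, side, and date of amputation", and also comorbidities.

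On size, section 2.10 states: "we will recruit 82 participants (41 per arm including both men and women").

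**The concern.** A subgroup contrast needs participants on both sides. Here the eligibility rule and the subgroup definition use the same two causes, one as the condition for entry and the other as one side of the comparison. Anyone who could be counted under 'others' is someone 2.5 keeps out.

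Two things are at stake. One of the three named subgroup factors has no analysable contrast as defined. In addition, a reader cannot tell from the document which section reflects the intended population. If 2.5 does, 2.18 needs a new definition. If 2.18 does, the eligibility criterion is wrong, and the recruiting sites screen against that criterion.

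**Working it through.** The core of the check is a comparison of two definitions. The arithmetic only sizes the consequence.

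**1. Who can be in each level**

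- Eligible by cause (2.5): dysvascular-related or diabetes-related.
- First level (2.18): diabetes and dysvascular. Read in line with section 1.1, which pools the two causes, this is the same set as the eligible population.
- Second level (2.18): every other cause. Its overlap with the eligible population is empty.

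The expected split is therefore 82 versus 0 at recruitment and 68 versus 0 at final assessment. With one level empty, the cause factor is constant and the treatment-by-cause term cannot be estimated.

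**2. The plan's own sample size, as background**

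Inputs from section 2.10: difference 13.6 m and SD 19.9 m on the two-minute walk test (reported as "at discharge from the rehab facility was 13.6 (19.9) m in adults with unilateral LLA"), two-sided alpha 0.05, power 80%.

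n per group = 2 × (1.96 + 0.84)² × (19.9 / 13.6)² ≈ 33.6, rounded up to 34. This matches the stated 34 per group. The recruitment figure follows as 68 × 1.2 = 81.6, rounded to 82. Neither figure depends on the cause subgroup.

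**3. What the contrast would offer if cause were not restricted**

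Assumption: the 91% in section 1.1, a figure for Canada as a whole, applies to this age group and these sites. The share with other causes is then 9%.

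- At recruitment: 0.09 × 82 = 7.4, about 7.
- At final assessment: 0.09 × 68 = 6.1, about 6.

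For o participants in 'others' out of N, with equal allocation within each level, the standard error of the difference between the two treatment effects is SD × √(4/o + 4/(N − o)). Approximate power for a difference in effect of 13.6 m is Φ(13.6/SE − 1.96).

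| N | o | SE | Power |
| --- | --- | --- | --- |
| 82 | 7 | 19.9 × √(4/7 + 4/75) = 15.7 m | 14% |
| 68 | 6 | 19.9 × √(4/6 + 4/62) = 17.0 m | 12% |

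If the share were twice as large (18%, about 15 of 82), SE = 19.9 × √(4/15 + 4/67) = 11.4 m and power would be about 22%. Over this range the contrast could be described but not usefully tested.

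These figures are on the two-minute walk scale because it is the only scale for which section 2.10 gives an SD.

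**The case against.** The best defence of the text is to read the first level as participants with both diabetes and dysvascular disease, and 'others' as those with only one. That split would not be empty. It is a strained reading, however: 2.18 defines no such split, and section 1.1 pools the two causes and reports them as one category. It does not remove the contradiction, although it does show that the wording needs attention.

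A second objection is that little is lost. No hypothesis, sample size, main analysis or stopping rule rests on this subgroup, and even with unrestricted entry it would hold about 7 people. This stands, and it limits how much weight the point deserves. It does not make the two sections compatible.

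A third objection is that a statistical analysis plan could redefine the contrast in time. It could. But this point is not about missing detail: the protocol itself fixes both the entry rule and the subgroup levels, and the two do not fit together.

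A reader might also draw three stronger inferences that the protocol does not support:

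- *That the commitment in 1.4 cannot be kept.* Section 1.4 promises attention to cause and names no 'others' group. Diabetic versus non-diabetic dysvascular amputation could meet that promise within the eligible population.
- *That the analysis will be quietly dropped or replaced once results are known.* Nothing in the document indicates this, and there is time to correct the definition beforehand.
- *That transtibial versus transfemoral could stand in for the contrast.* That is level of amputation, not cause, so it would add a different subgroup and not repair this one.

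**Conclusion.** The point holds. Under section 2.5 as written, the 'others' level in section 2.18 contains 0 of 82 participants, and the contrast by cause cannot be estimated. This rests on reading 'diabetes and dysvascular' as the pooled category used in section 1.1, and on enrolment that follows the stated criteria.

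The effect is confined to one of three named subgroup factors. It would be wrong to infer that the whole subgroup plan fails or that the primary result is at risk: the primary comparison and the sex and gender subgroups do not depend on this definition.

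The document does not settle which section is in error. Section 2.5 is explicit about cause, yet its own remarks on generalisability leave cause out, which would be an odd omission if the restriction were deliberate. The neutral conclusion is that the two sections must be reconciled.

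**What to change.** Reconcile 2.5 and 2.18 before any data are analysed, by one of two routes.

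- **If 2.5 states the intended population:** redefine the cause contrast in 2.18 within it, for example diabetes-related versus non-diabetic dysvascular amputation, and state how a participant with both conditions is classed. Otherwise remove the cause contrast. The cost is a sentence or two in 2.18. Cause and comorbidities are already collected at T1, but the protocol does not show the coding categories, so it should be confirmed that they allow the split.
- **If other causes are meant to be enrolled:** correct 2.5. This is a change to eligibility and so more than a wording edit, and the sites would need to be told. Section 2.18 should then state that about 7 of 82 participants are expected in 'others' if the 91% figure applies, and that the contrast is descriptive only.

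Neither route requires a change to the primary analysis.

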| What (materials) | Participants in SMART group will have access to the SMART platform for 10 weeks. SMART includes 6 modules, about 20 to 30 minutes in length, about the self-regulatory skills, managing mental wellness, physical health, residual limb management, managing a prosthesis, and managing daily living activities. Participants will receive a weekly 20-minute telephone contact from peers for 6 weeks to facilitate motivation using goal setting and action planning. There is also a *resource icon* that provides more information and resources, such as timeline after LLA, and funding for prostheses. |
| What (Procedures) | It is a multi-site parallel RCT at BC (Vancouver Costal Health, Fraser Health, Interior Health, Northern Health, and Vancouver Island Health), Toronto, ON (West Park Healthcare Centre & Sunnybrook Health Sciences Centre), and London, ON (Parkwood Hospital). The research coordinator will provide the contact information for each participant, to his or her trainer. The subjects in SMART group will receive online training on using the online SMART platform. An additional icon in SMART enables direct *private email contact to the trainer,* so that participant questions or problems are quickly addressed. The trainer will be a registered physiotherapist (PT) or occupational therapist (OT) with more than 5 years clinical experience who will arrange the first telephone call of peers. If there is also no online activity within one week through SMART by subjects, the trainer will call the subject to foster motivation and troubleshoot the potential technical problems. |
| Who provided | The trainer will spend less than 2 hours to provide instruction for a participant to learn how to use the SMART, at baseline (T1). The SMART platform will be asynchronously monitored through a web portal by the trainer, who will observe participant progress and provide feedback if required. If there is no online activity within a 7-day (consecutive) period, the trainer will contact the participant to inquire the reasons for inactivity and troubleshoot any problems including technical issues.  Two peers will be identified by our clinician partners at each study site. Peers are mentors with LLA who support the individuals with LLA.65 The assessor will be a trained research assistant who will be blinded to participants assigned groups. The assessor will evaluate all participants at baseline (T1), end of the intervention (6-weeks) (T2), and 4-week retention period (T3). |
| How (modes of delivery) | SMART is an online, educational and training platform for individuals with LLA that is asynchronously monitored by a trainer through a website. SMART will be delivered via computer or tablet with support of peers. |
| Where | Participants will use one module of SMART per week. All participants will be evaluated by an assessor online via Zoom (a secure, UBC-based platform) at T1, T2, and T3. |

**Appendix C:** Behavioural change techniques used for contents of modules in Self-Management for Amputee Rehabilitation Using Technology (SMART)

| **BCTs** | **Self-regulatory skills** | **Mental wellness** | **Physical health** | **Residual limb management** | **Managing a prosthesis** | **Managing daily living activities** |
| --- | --- | --- | --- | --- | --- | --- |
| Goal setting (behaviour) | * | * | * | * | * | * |
| Problem solving |  | * | * | * | * | * |
| Action planning |  | * | * | * | * | * |
| Self-monitoring of behaviour |  |  | * | * | * | * |
| Social support (practical) | * | * | * | * | * | * |
| Social support (emotional) |  | * | * | * | * | * |
| Instruction on how to perform a behaviour | * | * | * | * | * | * |
| Information about antecedents |  | * | * | * | * | * |
| Information about health consequences |  | * | * | * |  |  |
| Demonstration of the behaviour |  |  | * | * | * | * |

**Appendix D.** Brief Action Planning (BAP) Flowchart

Developed by Steven Cole, Damara Gutnick, Connie Davis, Kathy Reims

Accessed from: <https://centrecmi.ca/wp-content/uploads/2018/11/BAP_flow_Chart_2016-08-08.pdf>

[figure not shown]

**Appendix E.** Study flowchart

[figure not shown]

Supplement: S1 File — (DOC) [file pone.0278418.s002.doc]

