# 2. the proposed trial

**2.1 Study Design:**This is a Type 1 Effectiveness-Implementation Hybrid Design2 1:1 parallel single (assessor)-blinded randomized controlled trial (RCT) conducted online with participants from four Canadian sites (B.C.; London, ON; and two in Toronto, ON) to evaluate the 6-week effectiveness (and the 4-week retention effect) of SMART on patient-relevant outcomes, while documenting implementation factors.59Following the [RE-AIM](http://www.re-aim.org/) framework, a planning tool for implementation evaluation,60 we will assess the implementation of SMART. Also, a small end-of-trial qualitative study will be used to understand participants’ experience.61

**2.2 Trial Interventions:** Participants allocated to the intervention group will receive usual care after the LLA and access to **SMART**. We provide a detailed description of SMART using the TIDieR (Template for Intervention description and Replication) checklist62 provided in **Appendix B**. In **Appendix C** we provide a list of BCTs adopted for each module according to our systematic review and meta-analysis.41 Participants will access the SMART platform using their own computer/tablet, and will be screened for having a computer/tablet before enrolling in the study. In rare cases where a participant in B.C. does have a tablet, they may receive a tablet (Apple’s iPad) preloaded with a dedicated icon to enable direct connection with the SMART platform, if needed. Tablets will not be able to be provided to participants in Ontario.

**Content:** SMART is web-based eHealth intervention that has six educational and skill development modules. SMART is accessible through this link: <https://360.articulate.com/review/content/1afbca12-f6bb-465e-b40f-1029a6fa981b/review>

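### T3 is labelled post-intervention retention, but Appendix B leaves the SMART arm with platform access for all or part of that window

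*Protocol*

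**What the plan says.** Section 2.2 (Content) describes the product under test: "SMART is web-based eHealth intervention that has six educational and skill development modules". Section 2.6 gives its duration: "Participants in the SMART group will receive the intervention for six weeks". Section 2.9 fixes the assessments as "T2=within one week of completing SMART intervention" and "T3=retention period of four weeks post-intervention". Section 2.1 makes the later time point an aim, namely to "evaluate the 6-week effectiveness (and the 4-week retention effect) of SMART on patient-relevant outcomes", and section 1.2 repeats that aim.

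The What (materials) row of Appendix B adds something that the main text does not mention: "Participants in SMART group will have access to the SMART platform for 10 weeks". The same row limits the peer component: "Participants will receive a weekly 20-minute telephone contact from peers for 6 weeks to facilitate motivation using goal setting and action planning".

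Three further elements of the SMART arm carry no end date:
- the trainer's monitoring of the web portal, with feedback where needed (section 2.2, Delivery; Appendix B, Who provided);
- the contact triggered by inactivity: "If there is no online activity within a 7-day (consecutive) period, the trainer will contact the participant" (Appendix B, Who provided; similarly section 2.2);
- the email icon inside the platform that reaches the trainer (Appendix B, Procedures).

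The control arm's weekly contacts are capped at six in total (section 2.2, Control Intervention).

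**The concern.** If SMART is the platform, the protocol has it ending at week 6 in one place and still available up to week 10 in another. The word retention then has no fixed meaning. It could refer to what remains after the scheduled modules and peer calls stop, or to what remains after the platform is withdrawn. These are different quantities, and the text does not say which is meant.

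Continued access may also be more than passive. Read literally, a SMART participant who stops logging in during weeks 7 to 10 would be contacted after seven days, and the Procedures row of Appendix B gives motivation as one purpose of that call. The control arm has no counterpart after its six contacts. The four-weekly coordinator contact in section 2.14 applies to participants generally and does not even this out.

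At stake is the interpretation of a named objective. A T3 difference could be described as durability after a six-week programme when part of it may reflect continuing use. T3 is also the last time point, so the maintenance element of RE-AIM (section 2.8) has no later assessment to draw on. The Self-Report Habit Index is the outcome most exposed, because it is meant to capture automatic behaviour and its T3 value is hard to read if content and prompts may still be reaching one arm.

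**Working it through.** No formula beyond timeline arithmetic applies. Week 0 is the start of the first module week.

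**Inputs**
- Intervention: 6 weeks (section 2.6)
- Retention period: 4 weeks (section 2.9)
- T2: week 6 to week 7, because it may be held up to one week after completion (section 2.9)
- Platform access: 10 weeks (Appendix B)
- Start of the access clock: not stated. Let *s* be the number of weeks by which access opens before week 0. Values of 0, 1 and 2 are assumptions. Section 2.3 allows up to two weeks for baseline, randomisation and training, which makes an early opening plausible but does not fix it.

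**Base case.** 6 + 4 = 10, equal to the stated access period. With *s* = 0, access ends at week 10, which is also T3.

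**Overlap of access with the window**
- Window counted from week 6 (T3 at week 10): overlap = (10 − *s*) − 6 = 4 − *s*
- Window counted from a T2 held at week 7 (T3 at week 11): overlap = (10 − *s*) − 7 = 3 − *s*

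| Access opens before module week 1 (*s*) | Access ends | Overlap, T3 at week 10 | Overlap, T3 at week 11 |
|---|---|---|---|
| 0 weeks | week 10 | 4 of 4 weeks | 3 of 4 weeks |
| 1 week | week 9 | 3 of 4 weeks | 2 of 4 weeks |
| 2 weeks | week 8 | 2 of 4 weeks | 1 of 4 weeks |

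The overlap reaches zero only if access opens at least 4 weeks early (T3 at week 10) or at least 3 weeks early (T3 at week 11). Nothing in the protocol suggests either.

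**What stops and what may continue after week 6**
- Stops: the scheduled weekly modules, the peer calls and the control contacts.
- Continues for some or all of the window: platform access.
- Unknown: trainer monitoring, contact after inactivity, and email to the trainer.

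T3 therefore follows the end of the structured programme, but not clearly the end of access to SMART.

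**The case against.** The strongest reply is that access and delivery are different things. The delivered programme is one module a week plus weekly peer calls, and both end at week 6. Appendix B states the 10-week access and the 6-week peer calls in the same row, which looks deliberate, and its Who provided row still places T2 at the end of a six-week intervention and T3 after a four-week retention period. The protocol nowhere says that retention must follow withdrawal of the platform. Controls receive an education booklet, and nothing says they give it back, so both arms may keep reference material. Section 1.3 values online education partly because learners can return to it over time. Retention is also secondary to 6-week effectiveness, and the hypotheses in section 1.2 name no T3 contrast.

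Much of this stands. A reader might infer that T3 cannot show retention at all, or that the whole window is necessarily spent on treatment. The documents support neither inference. The scheduled components do stop, so T3 can show persistence after them. The start of the access clock is not given, and T3 could fall at or just after the end of access. Having access is not the same as using it, and use in weeks 7 to 10 is unknown.

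The reply does not remove the ambiguity. A reader of sections 2.6 and 2.9 alone would not learn that the platform stays open. A retained booklet is also not equivalent to a monitored platform with a trainer email link and an inactivity contact that have no stated end.

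**Conclusion.** The point holds in limited form. The protocol calls T3 post-intervention although the SMART arm has platform access for all or part of the preceding window: 4 of 4 weeks if access opens with the first module week and T3 is at week 10, and between 1 and 3 weeks under the other timings tabulated. T3 can show whether a difference persists after modules and peer calls end. It cannot separate that persistence from continued use of the platform.

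This rests on the stated 6, 4 and 10 weeks and on an assumed access start no more than two weeks before the first module week. No size can be put on any resulting distortion of the T3 difference, because the amount of use after week 6 is not known. The T2 comparison, the sample size and the interim analysis, which is tied to T2, are unaffected. The change should be made, but the main comparison does not depend on it.

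**What to change.** 1. Reconcile sections 2.6 and 2.9 with Appendix B. State when platform access starts and ends, and whether trainer monitoring, contact after inactivity and in-platform email continue after week 6. Which arrangement applies is for the investigators to decide.
2. If access runs into the T2 to T3 window, define the T3 contrast as the effect four weeks after modules and peer calls end, with continued platform access. Use that wording in sections 1.2, 2.1 and 2.9 in place of post-intervention retention.
3. Report SMART-arm portal use between T2 and T3. Section 2.2 already has the trainer monitoring the portal, and section 2.16 already plans to describe usage. This assumes that the usage records are dated.
4. Keep any display of T3 results by use purely descriptive. Use is self-selected after randomisation and occurs in one arm only, so such a split loses the randomised comparison and cannot recover a retention effect.

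The cost is a few sentences, a small amount of descriptive reporting and a slightly narrower retention claim. No new data collection or change to the assessment schedule is needed.
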